#### Physical and functional capacity assessment

##### 5RM leg press and knee extension

Multiple repetition strength assessments are associated with a lower risk of injury and symptoms of delayed muscle soreness as skeletal muscles, connective tissue and joints are exposed to lower loads than with maximal strength testing, such as 1RM;^76^ thus, 5RM testing is considered a more suitable assessment method within a rehabilitation setting for injured personnel. Therefore, unilateral muscle strength will be assessed using a dynamic 5RM test, defined as the maximal load (kg) that the participant can lift five times consecutively with the correct lifting technique. This will be performed on a leg press and knee extension machine to assess functional strength and is aligned with current clinical care practice. This test has demonstrated good test-retest reliability and can be used as a valid predictor of maximal strength.^77 78^ This outcome measure will be collected at T0_P1_ and T4_P1_, only, in Phase One.

##### Isometric mid-thigh pull

Isometric strength testing may provide a safer alternative for the quantification of force production relating to the elimination of painful joint movements under loaded conditions, thus offering clinical testing utility to those where pain is the primary limiting factor to performance.^79^,^81^ The isometric mid-thigh pull (IMTP) is currently implemented as a role fitness test within the British Army Physical Employment Standards, integrated into lower limb rehabilitation settings within UK Defence Rehabilitation,^79^ and has demonstrated good-to-excellent reliability in measuring maximal strength.^82^ The IMTP is a test that can assess multiple derivatives of maximal lower limb muscle force production capabilities, including peak force, rate of force development and limb symmetry, and will be delivered using a previously established, standardised testing procedure^80^ on a pair of portable force plates (Hawkin Dynamics, Portland, Maine, USA) located on the base plate of a mid-thigh pull rig (Absolute Performance, Cardiff, UK). Force-time data will be sampled at 1000 Hz and will be visually assessed against a previously established criteria, with invalid trials repeated.^80^ Isometric mid-thigh pull assessment will be completed at T1_P1_ and T4_P1_, in Phase One.

## Methods and analysis: Phase Two

### Study design

Phase Two is a 3-week, single-centre RCT embedded within DMRC Stanford Hall’s residential rehabilitation courses running from August 2025 to May 2026. Injured serving military personnel will be randomly assigned to one of the following groups: (1) low-load resistance training with either high-pressure or low-pressure BFR as determined by the outcome of Phase One or (2) standard residential rehabilitation (CON). The experimental treatment arm will be delivered alongside the 3-week residential rehabilitation course. The study design is outlined in figure 3.

**Figure 3 F3:**
[figure not shown]
Study design flow diagram: Phase Two. Phase Two timepoints—T0_P2_, baseline (day −3); T1_P2_, admission day (day 1); T2_P2_, daily (days 1–5, 6–10, 11–15); T3_P2_, start and end of residential rehabilitation weeks (days 1 and 5, 6 and 10, and 11 and 15); T4_P2_, end of intervention (day 15). BFR, blood flow restriction with resistance training; CON, standard residential rehabilitation/usual care group; DMRC, Defence Medical Rehabilitation Centre.

### Experimental intervention

Throughout the residential rehabilitation course, participants in the BFR group will have their standardised knee dominant exercises replaced with low-load BFR-RT at either high or low pressure. The decision as to which BFR pressure (ie, high or low pressure) will be implemented within Phase Two will be determined by a multistage process: (1) the pressure which elicits the greatest reduction in pain as per the primary outcome measure (BPI); (2) if no statistically significant difference is reported for pain, the pressure which promotes the greatest improvement in function as per the secondary outcome measure (LEFS) will be used; or (3) if no difference between groups for pain (BPI) or function (LEFS), the low-pressure group will be used due to greater tolerability and reduced perception of effort. The BFR group will complete 21× BFR-RT sessions over the 3-week residential rehabilitation course. Phase Two uses the same BFR protocol as in Phase One with only the number of sessions (21× vs 7× sessions) and study duration (3 weeks vs 1 week) changing. The control group will receive standard residential rehabilitation only, as described in table 1.

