## Abstract

**Background:**

Musculoskeletal injury (MSKI) is the leading cause of medical downgrading and discharge within the UK military, with lower limb MSKI having the greatest incidence, negatively impacting operational readiness. Pain is a primary limiting factor to rehabilitation progress following MSKI. Heavy-load resistance training (RT; ie, loads >70% 1-repetition maximum) is traditionally used but may be contraindicated due to pain, potentially prolonging recovery and leading to failure of essential physical employment standards for UK military personnel. Low-load RT with blood flow restriction (BFR) can promote favourable morphological and physiological adaption, as well as elicit hypoalgesia in healthy and clinical populations (eg, post-operative), and has proven a viable option in military rehabilitation settings. The acceptability and tolerance of higher relative BFR pressures in persistent pain populations are unknown due to the complexity of presentation and the perception of discomfort experienced during BFR exercise. Greater relative pressures (ie, 80% limb occlusion pressure (LOP)) elicit a greater hypoalgesic response in pain-free individuals, but greater perceived discomfort which may not be tolerated in persistent pain populations. However, lower relative pressure (ie, 40% LOP) has elicited hypoalgesia in pain-free individuals, which therefore may be more clinically acceptable and tolerated in persistent pain populations. The primary aim of both randomised controlled trials (RCT) is to investigate the efficacy and acceptability of using high-frequency, low-load BFR-RT in UK military personnel with lower limb MSKI where persistent pain is the primary limiting factor for progression.

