**Methodology:**

The presented protocol is a two-phase RCT based within a military rehabilitation setting. Phase One is a 1-week RCT to determine the most efficacious and acceptable BFR-RT protocol (7× BFR-RT sessions over 5 days at 40% or 80% LOP; n=28). Phase Two is a 3-week RCT comparing the most clinically acceptable BFR pressure, determined by Phase One (21× BFR-RT sessions over 15 days; n=26) to usual care within UK Defence Rehabilitation residential rehabilitation practices. Outcomes will be recorded at baseline, daily and following completion of the intervention. The primary outcome will be the brief pain inventory. Secondary outcomes include blood biomarkers for inflammation and pain (Phase Two only), injury-specific outcome measures, lower extremity function scale, objective measures of muscle strength and neuromuscular performance, and pressure pain threshold testing.

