**Trial registration number:**

Registered with Clinical Trials. The registration numbers are as follows: NCT06621914 (Phase One) and NCT06621953 (Phase Two).

STRENGTHS AND LIMITATIONS OF THIS STUDYThis novel two-phase study is based within a military residential rehabilitation setting with real-world outcomes and implications.Our two-phase study compares high versus low pressure blood flow restriction with resistance training (BFR-RT) over a 1-week period, to assess the acceptability and efficacy, before implementing the most accepted and efficacious pressure during a 3-week rehabilitation intervention where BFR-RT and usual care are compared with usual care alone.Our study combines objective (eg, neuromuscular strength, pressure pain threshold and temporal summation, blood biomarkers) and subjective (eg, patient-reported outcome measures) outcome measures to assess the acceptability, effectiveness and tolerability of BFR-RT.Our study only includes short-term follow-ups due to the nature of the studies, and the setting it is embedded within (ie, quick deployment upon return to home-unit).

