### Phase One RCT

A 1-week pilot RCT will determine the most effective and acceptable BFR-RT protocol in UK military patients, with the primary aim of reducing pain. This will be achieved by comparing two different BFR-RT pressures (high-pressure (80% LOP) vs low-pressure (40% LOP)) within a military residential rehabilitation setting. It is hypothesised that high-pressure BFR-RT will elicit a greater hypoalgesic response, but be less tolerable (ie, less total work completed with higher perception of effect).

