### Phase Two RCT

A 3-week RCT (resembling actual inpatient rehabilitation duration at DMRC) will compare the efficacy of the most clinically acceptable BFR pressure from Phase One to standard/conventional UK Defence Rehabilitation residential rehabilitation practice on physiological mechanisms underpinning changes in pain modulation and rehabilitation outcomes. It is hypothesised that the BFR-RT group will have greater reductions in pain, and increases in function, when compared with usual care alone.

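### The rule that picks the Phase Two pressure reads no Phase One tolerability result, so it cannot deliver the most acceptable pressure that the protocol says it carries forward

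*Protocol article*

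**What the plan says.** Several places in the protocol article make acceptability part of what Phase One decides. Under Study aims, Phase One RCT: "A 1-week pilot RCT will determine the most effective and acceptable BFR-RT protocol in UK military patients". Under Study aims, Phase Two RCT, the second trial "will compare the efficacy of the most clinically acceptable BFR pressure from Phase One". The abstract's Methodology paragraph describes Phase Two as "comparing the most clinically acceptable BFR pressure, determined by Phase One", and the strengths and limitations box speaks of testing both pressures "before implementing the most accepted and efficacious pressure during a 3-week rehabilitation intervention".

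The rule itself is under Methods and analysis: Phase Two, Experimental intervention. Stage 1 takes the pressure with the larger BPI reduction. Stage 2 applies "if no statistically significant difference is reported for pain, the pressure which promotes the greatest improvement in function", measured by the LEFS. Stage 3 applies if neither outcome differs: "the low-pressure group will be used due to greater tolerability and reduced perception of effort".

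On tolerability, the Phase One aims hypothesise that high pressure will relieve more pain "but be less tolerable (ie, less total work completed with higher perception of effect". (I read the last word as effort.) The Background section states that tolerance of higher pressures in persistent pain is not known. The Phase One section on patient-reported outcome measures provides a monitoring booklet for feasibility and tolerability. It records training load completed, session ratings of perceived exertion, and pain ratings before, immediately after and one hour after each session.

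**The concern.** The stated purpose and the operative rule do not match. A reader of the abstract or the aims would expect acceptability to help decide which pressure goes forward. Under the rule it never does.

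Stage 3 is the sharper case, because tolerability is its stated reason. It relies on the answer to a question that Phase One is meant to test, and it stands whatever the booklet shows.

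At stake are the experimental arm of Phase Two and what may be claimed about it. That pressure will be applied for 21 sessions and could be reported as the most acceptable one although acceptability played no part in choosing it.

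**Working it through.** No figure in the plan needs correcting. The check is to set the rule against the claims and follow each branch.

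**What each stage reads and can return**

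| Stage | Result used | Possible choice | Tolerability result used |
|---|---|---|---|
| 1 | BPI | 40% or 80% LOP | none |
| 2 | LEFS | 40% or 80% LOP | none |
| 3 | none (fixed default) | 40% LOP only | none, though tolerability is the reason given |

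**What is known about the premise of stage 3.** The Background section treats tolerance of higher pressures in persistent pain as unknown and low pressure as only possibly better tolerated. The abstract's Background paragraph attributes to high pressure "greater perceived discomfort which may not be tolerated in persistent pain populations", which is a possibility for this population and not a finding. The Phase One aims turn the difference into a hypothesis and define it: less total work and higher perceived effort. Stage 3 then uses it as established.

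**Whether the data exist.** Inputs are 28 recruited and 24 required (Sample size calculation), seven sessions (Phase One, Experimental intervention) and three pain-rating times per session (Phase One, Patient-reported outcome measures).
- Session records of work and exertion: 28 × 7 = 196, or 24 × 7 = 168 with 24 completers.
- Pain-rating occasions: 196 × 3 = 588, or 168 × 3 = 504.

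These counts show that both measures named in the hypothesis will be available. They do not show that any choice is wrong.

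**Where a tolerability reading could change the choice**
- A poorly tolerated 80% LOP can go forward only through stage 1 or 2, because stage 3 always returns 40%.
- At stage 3, suppose observed tolerability decided, with 40% kept if it did not separate the arms. If 40% is better tolerated, the choice is 40% under either rule. If the arms do not separate, it is again 40% under either rule. Only if 80% is better tolerated do the rules differ.
- Assume no true tolerability difference and a two-sided 0.05 test. One measure would then favour 80% by chance in 0.05 / 2 = 2.5% of stage-3 cases. Two measures in sequence would do so in at most 2.5% + 2.5% = 5%.

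**Wording of stage 2.** It takes the greater LEFS improvement and gives no criterion. Two observed means almost never tie exactly, so on a literal reading stage 3 would hardly ever be reached. Stage 3's own condition of no difference, together with the 0.05 level in Statistical methods and analysis, points to a significance requirement as the natural reading.

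**The case against.** The strongest reply is that the rule is sound as a decision rule. Reducing pain is the stated primary aim of Phase One, so putting BPI first is right, and efficacy is named alongside acceptability in most of the summary statements. A pre-set conservative default at 12 to 14 patients per arm is sensible. Its rationale also has some basis, since the abstract reports greater discomfort at high pressure in pain-free people. Poor tolerance may also show indirectly, because the Background says that benefit could be lost where pressure is not tolerated, and that would tend to reduce the BPI and LEFS gains. Finally, a tolerability reading at stage 3 alters the choice only if 80% LOP turns out better tolerated, against the protocol's own hypothesis.

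Most of this stands. It means the order of outcomes should stay and 40% should remain the default. It does not answer two things: the rule is described as yielding a property that it never examines, and a precaution is worded as a fact.

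A reader might infer more, and the documents do not support it:
- *That Phase Two is biased.* It is not. The pressure is fixed first, and Phase Two then randomises its own patients between that pressure and usual care.
- *That changing stage 3 protects patients from a poorly tolerated 80% LOP.* It does not, since that outcome arises only at stages 1 and 2, where leading with pain and function is the investigators' legitimate choice.
- *That the rule often picks the wrong pressure.* Nothing here measures that. How often stage 3 would be reached depends on assumed effects and correlations, and in any case it is not a rate of wrong choices.

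**Conclusion.** The point holds as a minor one. As written, the rule selects on pain, then function, then a precautionary default. It does not identify the most clinically acceptable pressure, and stage 3 asserts a tolerability advantage that the same document treats as unknown and under test. The effect is on what can be claimed about the chosen pressure and, in the uncommon case where 80% LOP proves better tolerated and neither BPI nor LEFS separates the arms, on the choice itself. The main conclusion rests on the text alone; only the 2.5% and 5% figures need the assumptions stated with them. The stage 2 wording is a smaller matter with an evident intended reading.

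**What to change.** Revise the selection paragraph as follows.
1. **Stage 2:** state that a statistically significant LEFS difference (two-sided p<0.05) is required, so that stage 3 can be reached.
2. **Stage 3:** use the observed Phase One tolerability measures that the hypothesis names, in a fixed order: total work completed, then session perceived exertion if work does not separate the arms. Judge separation at the plan's own 0.05 level. If neither measure separates them, use 40% LOP and call it a precautionary default, not a finding. Because the load is set from each patient's own maximum, work is best expressed relative to the amount prescribed.
3. **Description:** where stage 1 or 2 decides, say that the pressure was selected on pain or on function. Align the abstract and the Phase Two aim with this.
4. **Reporting:** show Phase One tolerability by arm beside the choice.

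If the choice has already been made (Phase Two was scheduled to start in August 2025), leave it as it is and apply items 3 and 4 only.

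The cost is one paragraph of wording and a slightly narrower claim about the chosen pressure. No new data are needed, since the booklet already collects them.

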### Outcome measures

#### Baseline characteristics

The same baseline characteristics as Phase One will be collected in Phase Two, at T0_P2_.

#### Patient-reported outcome measures

The PROMs used in Phase One (BPI, LEFS and injury-specific) will also be used within Phase Two, collected at T0_P2_, T3_P2_ and T4_P2_. Additionally, secondary outcome measures will be collected, including the Fatigue Assessment Scale, McGill Pain Questionnaire – Short Form, Pain Catastrophising Scale and Tampa Scale of Kinesiophobia. These secondary outcome measures will be collected at T0_P2_ and T4_P2_ only. The assessment of tolerability and daily response will again be monitored using the participant monitoring booklet (T2_P2_). The data collection schedule for all outcome measures can be found in online supplemental file 3.

#### Mechanistic pain measures

##### Pressure pain threshold

Following the same protocol as per Phase One, PPTs will be collected at T0_P2_–T4_P2_.

##### Temporal summation

Temporal summation is a form of quantitative sensory testing that uses mechanical pressure to gain insight into which pain mechanisms are involved for an individual patient.^83^ When used at local and remote sites of injured tissue, the assessment of temporal summation tests the function of A and C fibres, and their associated central pathways, and identifies the presence of local (peripheral sensitisation) and/or centrally driven symptoms (eg, secondary hyperalgesia).^83^,^85^ Central sensitisation, defined as increased nociceptive responsiveness following normal or subthreshold afferent input, may occur in different areas of the nervous system (eg, dorsal horn neurons),^86^ and current evidence suggests temporal summation is indicative of central sensitisation.^87^ Temporal summation assessment resembles the ‘wind-up’ effect, or second pain stimulus,^86 88^ often seen in persistent pain populations, by stimulating the unmyelinated C fibres.^89 90^ A measure of temporal summation will be taken at T0_P2_ and T4_P2_. To assess temporal summation, at the location closest to the individuals’ injured site from the previously described PPT test locations, 10 consecutive ramping pulses building to the mean pressure of the respective PPT score will be applied over 5 s with a 1 s hold, before immediate release, with 1 s rest interval before the next pulse. At the peak of each pulse, the participant will be asked to rate their pain on the NPRS scale. The first NPRS value will act as an anchor/baseline. Thereafter, each NPRS will be normalised via subtraction of the initial NPRS value. To reflect changes in temporal summation across the series, the NPRS epochs (mean NPRS rating of peaks; I 2–4, II 5–7 and III 8–10) will be calculated for the statistical analysis.^91^

##### Blood biomarkers

To date, there is limited literature investigating the effect of high-frequency BFR-RT on markers of inflammation and hypoalgesia.^92^ During Phase Two, 19× 10 mL venous blood samples from an antecubital vein will be collected at various timepoints to assess the acute and chronic effects of BFR-RT on hypoalgesia and inflammation, respectively. Beta-endorphin is a neuropeptide produced in the central nervous system and pituitary gland in response to pain or exercise^93^ and shares a similar structure to morphine and the same binding sites within the brain cells and receptors, thereby working as a powerful analgesic by inhibiting the communication of pain signals.^93^ Additionally, beta-endorphin has previously been used as an outcome measure within the BFR literature, with elevated levels reported following BFR-RT and BFR with aerobic exercise immediately post-intervention.^43 44^ Venous blood samples for beta-endorphin will be collected at T0_P2_, T2_P2_ (BFR only: Tuesday pre-intervention, immediately post-intervention, and 1-hour post-intervention, and Wednesday pre-intervention), T3_P2_ and T4_P2_. Inflammatory cytokines interleukin-6 and tumour necrosis factor-⍺ are thought to be drivers for the development of pathological pain^94^,^96^ and have been shown to have elevated levels in persistent pain populations^97^,^100^ and will be collected at T0_P2_, T3_P2_ and T4_P2_. To minimise pre-analytical variability within these biomarkers, all samples will be obtained at the same time of day (08:00–12:00), after a ≥12-hour fast and abstinence from alcohol (≥24 hours) and caffeine (≥12 hours).^101^ All samples will be centrifuged at 1000 × g for 15 min, within 30 min of sample collection. Plasma will then be separated into 1.5 mL aliquots and stored in snap-seal microcentrifuge tubes (Sarstedt, Germany) at −80°C. Samples will be analysed at the biochemistry laboratory at Northumbria University using commercially available ELISA kits.

### Physical and functional capacity assessment

#### 5RM leg press and leg extension

Following the same protocol as per Phase One, 5RM assessment will take place at T0_P2_ and T4_P2_.

#### Isometric mid-thigh pull

Following the same protocol as per Phase One, IMTP assessment will take place at T0_P2_, T3_P2_ and T4_P2_.

## Discussion

The utility of BFR exercise is expanding across numerous clinical populations,^102^,^104^ with multisystem beneficial adaptions being increasingly reported (eg, cardiovascular, morphological and neural).^105^,^108^ Numerous studies have investigated BFR-RT utility over 6–8 weeks, with two to three sessions per week, mirroring a traditional rehabilitation approach, focusing on physiological adaption rather than pain.^37 109 110^ Additionally, Ladlow *et al*^21^ provided rationale for high-frequency usage within military rehabilitation settings; however, significantly less research has investigated high-frequency BFR-RT in inpatient setting when pain is the primary outcome measure. This two-phase research programme aims to expand upon the previous and currently ongoing UK Defence Rehabilitation RCT.^21 50^ To our knowledge, this two-phase RCT will be the first to assess the effect of high-frequency BFR-RT, and BFR-RT in general, on pain modulation in military personnel with lower limb MSKI. The clinical implications of these findings are that BFR-RT could be a rehabilitation intervention that can induce beneficial clinical adaptions and attenuate pain response, in the absence of high mechanical loads and pharmacological intervention, respectively. This study aims to optimise rehabilitation outcomes when hypoalgesia is the primary focus of treatment. If efficacy is established, BFR therapy for the management of MSKI associated pain could be applied across UK Defence Rehabilitation settings. The results of this study will provide insight and knowledge applicable to the wider clinical and scientific community, including those in civilian and professional sports settings.

